**3.3.3 Exploratory outcome measure**

Change from baseline in serum prolactin level.

**3.4 Safety**

Participation in this study is considered to be safe. However, there are certain side effects of Cabergoline that need to be taken into account. The most common and severe side effects are mentioned below. To ensure participant safety, phone calls are scheduled after four and eight weeks, specifically inquiring about side effects. Throughout the trial, participants can contact one of the trial coordinators if they experience any side effects from the trial medication. Participants can continue to contact the trial coordinators with concerns about side effects up to four weeks after the final visit and the end of treatment (the substance is considered to be out of the body after 14 days; 5 x the half-life of Cabergoline).

**3.4.1 Cabergoline**

I this trial, participants randomized to cabergoline treatment will recieve 0.5 mg/week, totaling 6 mg throughout the trial period. Cabergoline side effects are dose-dependent. According to the product summary, the following side effects have been reported:

Very common (> 10%): Nausea, dyspepsia, gastritis, abdominal pain, fatigue, headache, dizziness.

Common (1 - 10%): Constipation, vomiting, depression, asymptomatic hypotension.

In extremely rare cases, fibrotic diseases, including pericardial and pulmonary fibrosis, have been reported, and a possible association between Cabergoline treatment and fibrotic heart valve disease has been suggested. The association has been observed in Parkinson's patients of advanced age and comorbidity after prolonged high-dose treatment (3 mg/day for more than 6 months ≈ 540 mg). The accumulated dose in this project is 6 mg. Recently, the British Society of Echocardiography, the British Heart Valve Society, and the Society for Endocrinology, based on a review of existing literature, concluded that there is extremely limited evidence that treatment with dopamine receptor agonists at doses used in the treatment of hyperprolactinemia can cause heart valve disease [25].

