**2.3 Treatment of migraine**

The pharmacological management of migraine encompasses acute and preventive strategies, often necessitating a combination of both [9]. Triptans, which selectively activate serotonergic 5-HT1B and 5-HT1D receptors, constitute the primary medications for acute treatment [10]. In the realm of preventive treatment, commonly employed agents include beta-blockers, angiotensin II antagonists, and antiepileptics. Notably, novel therapeutic approaches involve the use of human antibodies targeting calcitonin gene-related peptide (CGRP) and the CGRP receptor, demonstrating efficacy in both acute and preventive settings [11]. Treatment with CGRP antibodies, however, carries a substantial economic burden, and consequently, their utilization in Denmark is limited to prophylactic treatment for chronic migraine in adults, specifically following inadequate response to previous preventive therapies.

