**3. Methods**

**3.1.1 Design**

This trial is a prospective, randomized, double-blind, placebo-controlled pilot study testing the hypothesis that in patients with migraine, cabergoline 0,5 mg weekly will reduce number of monthly migraine days (MMD) more effectively than placebo. Participants will be randomized to treatment with cabergoline 0.5 mg once weekly or placebo in addition to any existing migraine treatment and followed up after three months (12 weeks) of intervention.

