**3.1.3 Study program**

The study consists of a 4-week baseline period during which participants will fill out a daily electronic headache diary, first visit (day 1) comprising 2 x questionnaires and blood samples, 12 weeks treatment period during which participants will fill out a daily electronic headache diary, followed by the last visit comprising 2 x questionnaires, PGIC and blood samples. To ensure participant safety and promote compliance, participants will be contacted by phone after four and eight weeks.

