**3.2.3 Exclusion criteria**

- Known or suspected heart valve disease
- Severe untreated hypertension
- Treatment-requiring psychiatric diagnosis
- Treatment with dopamine receptor agonists
- Treatment with medications known to interact with cabergoline (dopamine D2 receptor antagonists, macrolides, and itraconazole)
- Pregnant or breastfeeding women.
- According to Investigator discretion individuals deemed unlikely to comply with prescribed study procedures, restrictions, or prerequisites will be excluded. Additionally, the Investigator possesses the authority to identify and exclude, at their discretion, any conditions that may render a participant's involvement in the study unsafe or inappropriate.

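### The protocol names asymptomatic hypotension as a common side effect and excludes severe untreated hypertension, but specifies no blood pressure measurement, and its side-effect enquiry cannot find an effect without symptoms.

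*Protocol*

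**What the plan says.** Section 3.4.1 (Cabergoline) introduces its list with "Cabergoline side effects are dose-dependent. According to the product summary, the following side effects have been reported". The second tier of that list reads "Common (1 - 10%): Constipation, vomiting, depression, asymptomatic hypotension".

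Section 3.4 (Safety) gives two ways of learning about side effects. The active one is that "phone calls are scheduled after four and eight weeks, specifically inquiring about side effects". The passive one is that "participants can contact one of the trial coordinators if they experience any side effects from the trial medication", an offer that stays open for four weeks after the end of treatment. The Safety row of the synopsis says the same.

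Section 3.1.3 (Study program) describes a first visit on day 1 with two questionnaires and blood samples, then the treatment period, "followed by the last visit comprising 2 x questionnaires, PGIC and blood samples". Section 3.5 (Pregnancy) adds a pregnancy test at the first visit for fertile women. No section mentions blood pressure or vital signs as a procedure.

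Section 3.2.3 excludes "Severe untreated hypertension" and gives no reading, definition or source. Section 3.2.4 (Dropout) makes the exclusion conditions grounds for withdrawal during the trial as well.

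**The concern.** A side effect that is asymptomatic by definition is not something a participant experiences, so it will not come up in a telephone call or prompt a participant to make contact. The protocol names this risk and then describes a collection method that cannot observe it. The other listed common effects either produce complaints or can be asked about. This one has to be measured.

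Two things are at stake. First, a report of no hypotension in either arm would reflect how side effects were sought, and a reader could take it as reassurance. Section 4.3 gives the detection of potential problems as one purpose of the pilot's size, so the gap touches something the trial says it is for. Second, the hypertension exclusion depends on knowing a patient's blood pressure status, and the protocol does not say where that knowledge comes from. Section 3.2.1 recruits partly through the hospital's Facebook page, so hospital records showing blood pressure cannot be assumed for every patient.

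**Working it through.** **Side-by-side check.** The protocol's own statements on this point are:

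| Item | Section | Content | Blood pressure specified? |
|---|---|---|---|
| Named risk | 3.4.1 | Asymptomatic hypotension, 1-10% | n/a |
| Active collection | 3.4 | Telephone enquiry, weeks 4 and 8 | No |
| Passive collection | 3.4 | Contact started by the participant | No |
| First visit | 3.1.3, 3.5 | Questionnaires, blood samples, pregnancy test where relevant | No |
| Last visit | 3.1.3 | Questionnaires, PGIC, blood samples | No |
| Hypertension exclusion | 3.2.3 | Condition named, no source | No |
| Withdrawal on exclusion conditions | 3.2.4 | Refers back to the exclusions | No |

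The pregnancy exclusion has a named test at a named visit. The hypertension exclusion has neither.

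**Scale.** The protocol gives no expected number of hypotension cases, so there is no figure to reproduce. The inputs are n = 18 on cabergoline (section 4.3; 36 / 2 under 1:1 allocation) and p = 0.01 to 0.10 (section 3.4.1). Applying this p to the trial dose is an assumption.

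Expected cases = n × p:
- p = 0.01: 18 × 0.01 = 0.18
- p = 0.05: 18 × 0.05 = 0.90
- p = 0.10: 18 × 0.10 = 1.80

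Chance of at least one case = 1 − (1 − p)^n:
- p = 0.01: 1 − 0.99^18 = 16.5%
- p = 0.05: 1 − 0.95^18 = 60.3%
- p = 0.10: 1 − 0.90^18 = 85.0%

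With 15 patients in the arm (half of the 30 in the section 4.3 rule of thumb), the chance runs from 1 − 0.99^15 = 14.0% to 1 − 0.90^15 = 79.4%.

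So at the labelled frequency at least one case is plausible, though not assured. The argument does not depend on p: the planned collection method would not find the effect at any rate, apart from a chance reading taken outside the protocol.

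**The case against.** The best counter-argument is that this is silence, not contradiction: no two sentences conflict, and a hospital visit may well include a blood pressure reading that nobody wrote down. Part of this stands. Section 3.1.3 is not a complete list, because the pregnancy test appears only in section 3.5. A reader might infer that blood pressure is never measured. The documents support only that no measurement is specified.

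Other stronger readings also go too far:

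- **The 1-10% as a rate for this trial.** It comes from the product summary, and the protocol calls side effects dose-dependent. The rate at 0.5 mg weekly in migraine is unknown.
- **A wrong tolerability conclusion.** Sections 3.3.1 to 3.3.3 list no tolerability or blood pressure outcome, so there is no planned conclusion to be wrong. What is lost is the meaning of an absence of reports.
- **The exclusion applied by history alone.** The protocol names no source at all, and records are possible. Other medical exclusions, such as heart valve disease, also appear without a test, and section 3.2.3 gives the investigator wide discretion to exclude.
- **Blood-pressure-lowering co-treatment as expected.** Study drug is given "in addition to any existing migraine treatment", and section 2.3 says that in prevention "commonly employed agents include beta-blockers, angiotensin II antagonists, and antiepileptics". This makes such co-treatment possible. Nothing says how many participants would be taking it.

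It is also fair to say that dizziness, which the protocol lists, can be reported by telephone, so hypotension that causes symptoms may surface. That does not help with the asymptomatic form, which is the one named. The objections narrow the point but leave the mismatch between stated risk and stated method in place.

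**Conclusion.** The point holds in a limited form. The protocol names a side effect that its stated collection method cannot observe, and it sets an exclusion, carried into the withdrawal rules, with no stated reading or source. An absence of reported hypotension would be uninformative, and undiagnosed hypertension could pass unnoticed at entry. The documents do not show that it would.

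The consequence is confined to safety ascertainment and eligibility. The primary endpoint, its analysis and the sample size are untouched. The 0.18 to 1.8 expected cases are illustrative and rest on carrying a product-summary frequency over to this dose. The point also assumes that no reading is specified in a trial document outside the protocol. Visit procedures and eligibility checks belong in the protocol, so this is not a matter left to a statistical analysis plan.

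**What to change.** Reconcile sections 3.1.3, 3.2.3, 3.4 and 3.4.1. There are two ways to do it, and the choice is the sponsor's.

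1. List a blood pressure reading among the procedures of the two existing visits (day 1 before the first tablet, and the last visit), and report the change by arm descriptively.
2. Otherwise, state which source is used for the hypertension exclusion, and state plainly that asymptomatic hypotension is not assessed, so that an absence of reports is not read as evidence.

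The first option costs a few minutes at each of two visits that already take place, plus one line on the case report form. It needs no extra visit or patient. It is only a partial remedy, because two readings 12 weeks apart would miss transient falls in between. The second option costs two sentences, and it is the only one left if the visits have already been held. No blood pressure threshold, dose action, eligibility rule or subgroup analysis is proposed.

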**3.5 Pregnancy**

Taking Cabergoline during pregnancy or while breastfeeding is discouraged. Pregnancy should be avoided for at least 1 month after treatment is completed due to the drug's long half-life and limited available data on fetal exposure. During the first visit, fertile female participants must undergo a pregnancy test and during the trial and one month afterward, they must use reliable contraception (intrauterine device or hormonal contraception; birth control pills, implants, transdermal patches, vaginal rings, or depot injections).

In this context, a woman is considered fertile from menarche to menopause, unless she is permanently sterilized. Permanent sterilization methods include hysterectomy, bilateral salpingotomy, and bilateral oophorectomy [26].

**4. Statistics and data management**

The data will be collected at Steno Diabetes Center, Aarhus University Hospital, Denmark where data management work and statistical analyses will be performed.

**4.1 Statistical analysis**

Differences between study groups will be assessed with unpaired t-tests or using non-parametric statistics as appropriate. Ordinal variables will be assessed with chi-2 test for trend or Mann-Whitney U test and Pearson’s chi-square test or Fisher's exact test will be used to test differences between proportions. Two-sided statistical significance levels of 5% will be used and estimates will be presented with 95% confidence intervals.

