**3.1.2 Randomization**

Thirty-six patients will be randomized to receive treatment with 0.5 mg Cabergoline or placebo once a week. The randomization is conducted in a 1:1 ratio in 2 blocks of 18 patients and performed by the Aarhus University Hospital Pharmacy. The corresponding order of numbering and treatment assignment is specified in a randomization list, which is kept at the Service Production Hospital Pharmacy throughout the entire process. The Hospital Pharmacy also labels both the investigational drug and the placebo. Along with the investigational drug, the Hospital Pharmacy provides sealed code envelopes (corresponding to the randomization) that can be broken for individual participants if it is necessary for the investigator to know the assigned treatment.

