**3.3 Endpoints**

**3.3.1 Primary endpoint**

The primary endpoint was change in MMD between the baseline period and the final 28 days of the treatment period. A migraine day is defined as any calendar day on which the participant has onset, continuation, or recurrence of migraine as recorded in the electronic diary. MMD was defined as number of migraine days per 28 days.

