**3.3.2 Secondary endpoints**

- ≥ 50% reduction in MMD
- Patient global impression of change (PGIC) measured on a numerical rating scale 0-10 (Likert scale 0-10; where 0=very much worse, 10=very much better, 5=no change)
- use of acute migraine–specific medication (triptans)
- change from baseline in MIDAS score and HIT-6 score

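### Section 4.1 compares change in MMD without baseline adjustment; an analysis of covariance on the diary baseline would usually be more precise at almost no cost

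*Protocol*

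**What the plan says.** Section 3.3.1 defines the primary endpoint as "change in MMD between the baseline period and the final 28 days of the treatment period". Section 3.1.3 supplies the baseline: "The study consists of a 4-week baseline period during which participants will fill out a daily electronic headache diary". The secondary endpoints in section 3.3.2 include "change from baseline in MIDAS score and HIT-6 score".

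Section 4.1 holds the only analysis text for continuous outcomes: "Differences between study groups will be assessed with unpaired t-tests or using non-parametric statistics as appropriate". It names no covariate, does not say which of the two options is primary, and does not name the non-parametric method. It adds that "Two-sided statistical significance levels of 5% will be used and estimates will be presented with 95% confidence intervals". It does not mention the primary endpoint by name; that the sentence covers it is inferred, because no other text does.

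Section 3.1.2 states that "The randomization is conducted in a 1:1 ratio in 2 blocks of 18 patients" and mentions no stratification by baseline MMD. Section 4.3 sets 18 patients per arm without an SD, an effect size or a power.

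**The concern.** A change score uses the baseline, but with a fixed coefficient of 1. Patients enter because they have more than six migraine days a month, so some regression to the mean is expected and the slope of follow-up MMD on baseline MMD is likely to be below 1. In that case subtraction over-corrects, which has two consequences:

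- The difference between arms has a larger variance than a baseline-adjusted difference.
- If the arms differ at baseline by chance, part of that gap passes into the estimated effect. An active arm that starts higher looks better than it should, and one that starts lower looks worse.

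At 18 per arm precision is scarce, and neither the allocation nor the analysis as written controls for baseline MMD.

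**Working it through.** **The plan's own figure.** Section 4.3 starts from a conventional minimum of 30 and allows for 20% dropout: 30 × 1.2 = 36, or 18 per arm. (Dividing instead gives 30 / 0.8 = 37.5.) There is no power calculation to reproduce.

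**Inputs.** From the protocol: n = 18 per arm, N = 36, 1:1 allocation, two-sided 5%. Assumed, because the protocol gives neither: the correlation r between baseline and final MMD (range 0.3 to 0.8), and the ratio k of follow-up SD to baseline SD (1 in the main case; 0.8 and 1.2 as alternatives).

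**Formulas.** With the baseline SD as unit, the residual variances per patient are:

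- change score: 1 + k² − 2rk
- ANCOVA: k²(1 − r²)

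The difference is (1 − rk)², which is zero only when the slope rk equals 1. With k = 1 the ratio of ANCOVA to change-score variance is (1 − r²) / [2(1 − r)] = (1 + r)/2. Estimating the slope multiplies it by about 1 + 1/(N − 4) = 1 + 1/32 = 1.031.

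**Precision with equal SDs, 18 per arm.**

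| r | (1 + r)/2 | after slope penalty | change-score trial of equal precision (18 / ratio) |
|---|---|---|---|
| 0.3 | 0.65 | 0.67 | about 27 per arm |
| 0.5 | 0.75 | 0.77 | about 23 per arm |
| 0.7 | 0.85 | 0.88 | about 20.5 per arm |
| 0.8 | 0.90 | 0.93 | about 19 per arm |

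With 15 per arm after dropout, the penalty is 1 + 1/26 = 1.038 and the ratios at r = 0.3, 0.5 and 0.7 become 0.675, 0.779 and 0.883.

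Simulation (8,000 trials per value of r) took an effect that the change-score test should detect with about 80% power. Power for change score and ANCOVA was 78% and 91% at r = 0.3, 77% and 87% at r = 0.5, and 78% and 83% at r = 0.7. With no effect (4,000 trials per value), the change-score test rejected in 4.4% to 4.9% of trials and ANCOVA in 4.6% to 4.7%.

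**Precision with unequal SDs.**

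- k = 1.2, r = 0.7: 1.44 × 0.51 / (2.44 − 1.68) = 0.966; with the penalty 0.997.
- k = 1.2, r = 0.8: 1.44 × 0.36 / (2.44 − 1.92) = 0.997; with the penalty 1.028, so ANCOVA is very slightly worse.
- k = 0.8, r = 0.5: 0.64 × 0.75 / (1.64 − 0.80) = 0.571; with the penalty 0.589.

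**Chance imbalance.** The between-arm difference in mean baseline MMD has an SD of √(2/18) = 0.33 baseline SD. The probability of a gap above 0.5 SD is P(|Z| > 0.5/0.333 = 1.5) = 13%. At 15 per arm the figures are 0.37 SD and 17%. Given a gap d and equal SDs, the change-score difference is off by −(1 − r)d. For d = 0.5 SD that is 0.35, 0.25 or 0.15 SD at r = 0.3, 0.5 or 0.7. With an assumed SD of 4 days, the gap is 2 days and the error 1.4, 1.0 or 0.6 days.

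**Interval width at the same assumed SD of 4 days.** The 95% half-width is 3.2 days for change score and 2.6 for ANCOVA at r = 0.3, 2.7 and 2.4 at r = 0.5, and 2.1 and 2.0 at r = 0.7.

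**The case against.** The strongest reply is that nothing in section 4.1 is invalid. An unpaired t-test on change is a standard analysis. Randomization makes it unbiased, its type I error holds, and its interval already contains the variability due to baseline imbalance. That stands. A reader might infer that the estimate is biased or that the diary baseline is wasted; the protocol supports neither. The endpoint subtracts the baseline, and the imbalance error exists only conditional on the baselines actually drawn. A large gap is also not the expected outcome: one above 0.5 SD has about a 13% chance.

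The size of the gain is uncertain too. It depends on r and k, which the protocol does not give. The entry threshold cuts off low baseline values and could make the follow-up SD the larger of the two, in which case the gain may be negligible. That also stands, and is why a range is shown.

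A third reply is that the choice of test may be settled in a statistical analysis plan. For the rule between t-test and rank test, that is fair. A reader might infer that the test will be picked after the data are seen, but section 4.1 gives no timing. Likewise, the missing baseline reference for triptan use in section 3.3.2 is a definition that an analysis plan can complete. The reply does not reach the main point: on adjustment the protocol is not silent, since the t-test it names is unadjusted.

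Finally, the trial is a pilot sized without a power claim, so no stated power is broken. But section 3.1.1 states an efficacy hypothesis and section 4.1 tests at 5%, so precision still matters.

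**Conclusion.** The point holds as an improvement in efficiency, not as an error of validity. The protocol states an unadjusted comparison where the baseline needed for a usually more precise one is already collected. With equal SDs and r between 0.3 and 0.8, ANCOVA lowers the variance by about 33% to 7%, net of the slope penalty. It also removes, apart from error in the estimated slope, the shift that a chance baseline gap puts into the change-score difference. The conclusion rests on an assumed r and an assumed SD ratio. The benefit grows if MMD varies less at follow-up than at baseline, and practically vanishes when the slope on baseline is near 1. Even then, the loss from adjusting is only about 3% of variance.

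**What to change.** In section 4.1, name one primary analysis: ANCOVA of final 28-day MMD on treatment and baseline MMD, reported as an adjusted mean difference with its 95% confidence interval. Using change in MMD as the response gives the same treatment estimate, so the endpoint in section 3.3.1 can stay as it is. Keep one rank-based test, identified by name, as a sensitivity analysis. Use the same baseline adjustment for MIDAS and HIT-6, which are already defined as changes from baseline.

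The cost is one sentence and one estimated slope, about 3% of variance at N = 36. No further data or visits are needed.

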**4.2 Analysis population**

The results will be analyzed according to a modified intention-to-treat principle comprising all patients who undergo randomization and receive the study treatment. Patients who withdraw fter receiving the first study treatment will be censored at the date of withdrawal of consent. Patients who are lost to follow-up will be censored on the day of last study visit. Protocol violations will be monitored continuously. Data collected during the study will be coded so that no subjects can be identified.

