**3.2.4. Dropout**

Participants can withdraw from the trial at any time without consequences for their future treatment. Data obtained from a withdrawn participant will be utilized, if possible – it depends on when in the study a given participant withdraws. Patients will be withdrawn from the study if:

- The participant wishes to withdraw.
- The investigator determines that the participant cannot adhere to the trial procedures.
- The participant develops severe or intolerable side effects. In such cases, the trial will be stopped for the individual participant, and the investigator will arrange relevant follow-up, including referral for appropriate treatment.
- Conditions arise as described under 'Exclusion Criteria'.
- Changes in the established migraine treatment.
- Pregnancy.

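### Section 4.2 censors patients on a 28-day change score, where censoring has no defined meaning, and its lost-to-follow-up rule discards recorded diary days

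*Protocol*

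**What the plan says.** Endpoint (Protocol 3.3.1): "The primary endpoint was change in MMD between the baseline period and the final 28 days of the treatment period". The scale is given as "MMD was defined as number of migraine days per 28 days".

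Test (4.1): "Differences between study groups will be assessed with unpaired t-tests or using non-parametric statistics as appropriate".

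Analysis set (4.2): a modified intention-to-treat set of everyone randomized who receives study treatment. Two rules follow for patients who leave:
- Withdrawals: "Patients who withdraw fter receiving the first study treatment will be censored at the date of withdrawal of consent".
- Lost patients: "Patients who are lost to follow-up will be censored on the day of last study visit".

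Schedule (3.1.3): a first visit on day 1, a daily electronic diary through 12 weeks of treatment, "followed by the last visit comprising 2 x questionnaires, PGIC and blood samples". The contacts at weeks 4 and 8 are by phone.

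Dropout (3.2.4): data from a withdrawn participant are used where feasible, and "it depends on when in the study a given participant withdraws". Section 4.3 expects at most 20% dropout.

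**The concern.** Censoring belongs to time-to-event analysis, where a patient contributes follow-up time up to a date. No endpoint in 3.3 is a time to an event, and no test in 4.1 takes a censoring time. An analyst following 4.2 cannot tell what value, if any, a censored patient contributes to the comparison of changes.

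The lost-to-follow-up sentence goes further. It ties the cut-off to the last visit, although the outcome comes from a daily diary and there is no visit between day 1 and the end of week 12. Recorded outcome data are thrown away. Two patients with identical diaries are also treated differently: one who withdraws consent keeps the days up to that date, and one who is lost keeps nothing after day 1.

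At stake are precision in a trial of 36 and the match between the declared analysis set and the patients who actually supply a value. If the reasons for leaving differ between arms, the estimated difference is at stake too. The protocol makes this plausible: 3.2.4 lists intolerable side effects and changes of established migraine treatment as grounds for withdrawal.

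**Working it through.** **1. The plan's own figure.** Section 4.3 takes 30 patients and allows for 20% dropout: 30 × 1.20 = 36, or 18 per arm. This reproduces the stated number. (Dividing instead gives 30 / 0.80 = 37.5.) The point made here does not affect the sample size. At the stated maximum, 0.20 × 36 = 7.2 patients leave and 28.8 remain.

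**2. Diary days dropped for a lost patient.** Treatment lasts 12 × 7 = 84 days. For a full course the final 28 days are days 57 to 84. The last visit before loss is day 1, so only day 1 is kept. This assumes that the diary was filled in until the patient was lost.

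| Lost at | Diary days recorded | Dropped (recorded − 1) | Dropped days in final window (recorded − 56) |
|---|---|---|---|
| week 4 | 28 | 27 | 0 |
| week 8 | 56 | 55 | 0 |
| week 11 | 77 | 76 | 21 |

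Counting the phone calls as visits would not fully cure this. Loss at week 11 would then be cut at day 56, and the same 77 − 56 = 21 final-window days would go.

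**3. Withdrawals.** Diary days up to the withdrawal date can be kept. With the window fixed at days 57 to 84, withdrawal by week 8 leaves 0 of 28 window days. Withdrawal at week 9, 10 or 11 leaves 7, 14 or 21.

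**4. Precision.** The protocol gives no SD or power, so this is in SD units (two-sample t-test, two-sided 5%, 80% power). The detectable difference is 0.96 SD with 18 against 18, and 1.08 SD with 15 against 14. The first figure is a best case, since early diary months recover only part of a missing final value.

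**5. Bias if only completers are compared.** All inputs in this step are assumptions: SD 4 days, equal correlation ρ of 0.5 to 0.7 between periods, true difference −2.0 days, 20% dropout.

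- Let placebo patients in the worse half of month-1 change leave with probability 0.38 and the better half with 0.02 (mean 0.20), while dropout on cabergoline is random at 20%.
- Placebo completers are then 0.98 / 1.60 = 0.6125 from the better half and 0.62 / 1.60 = 0.3875 from the worse half.
- SD of change = 4 × √(2(1 − ρ)) = 4.00 at ρ = 0.5 and 3.10 at ρ = 0.7. Month-1 and month-3 changes share the baseline and correlate (1 − ρ) / (2(1 − ρ)) = 0.5. The mean of a half-normal is √(2/π) = 0.798 SD.
- Shift in the placebo mean = 0.5 × (0.6125 − 0.3875) × 0.798 × SD of change = 0.0898 × 4.00 = 0.36 days, or 0.0898 × 3.10 = 0.28 days, towards apparent improvement.
- The estimated difference becomes −1.64 or −1.72 instead of −2.0.

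Simulations of this kind of scenario, with varying dependence of dropout on response, averaged −1.45 to −1.72. That is a shift of 0.28 to 0.55 days, summarized below as roughly 0.3 to 0.5. With random dropout in both arms the average stayed at about −2.0. With the same outcome-driven rule in both arms the shift ran from none to about 4% (0.04 × 2.0 = 0.08 days). For scale, with 14.4 completers per arm the standard error is SD of change × √(2 / 14.4), which is 1.49 days at ρ = 0.5 and 1.15 at ρ = 0.7.

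**The case against.** The strongest reply is that the withdrawal sentence does no harm. It can be read as a consent cut-off: keep what was recorded up to that date and use nothing later. That loses no recorded day and agrees with 3.2.4. This stands, so the data-discarding argument applies to lost patients only, and the protocol does not say what share of the 20% they make up.

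A reader might infer that the trial is bound to become a completers analysis. The protocol does not say so. Nothing in 4.2 excludes patients without a final value, and a method for missing data may stand in a statistical analysis plan that is not shown. Because the scale is a count per 28 days, a partly recorded window could be prorated. Section 3.3.1 also gives no day numbers for the window, so days 57 to 84 is the natural reading but not a written one for early leavers.

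A reader might also infer that dropouts leave the denominator of the 50% responder endpoint, or that the treatment effect will be understated by a known amount. The first is written nowhere. The second rests on one assumed scenario in which dropout works differently in the two arms, and even there the shift is small beside the standard error.

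None of this rescues the lost-to-follow-up sentence. It is a rule that the protocol states, not a gap left to the analysis plan. A plan that used all diary days would contradict it.

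**Conclusion.** The point holds in this form. Censoring has no defined meaning for this endpoint and these tests, and the rule for lost patients, read with the visit schedule, removes recorded diary data after day 1, including up to 21 final-window days for loss at week 11. Such patients have no post-baseline value while being counted in the modified intention-to-treat set. Unless a missing-data method is specified, the analysis is close to a completers analysis for up to about 7 of 36 patients. That is an upper limit, since 20% is the stated maximum for dropout of every kind.

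The size and direction of any bias depend on why patients leave, as the scenarios above show; roughly 0.3 to 0.5 days comes from a single set of assumptions and is not a forecast. The trial is a self-described pilot and the remedy is wording, so this is a should-fix.

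**What to change.** In 4.2, replace the lost-to-follow-up sentence with a rule that uses all diary days up to the patient's last entry. Reword the withdrawal sentence as a data cut-off: data up to withdrawal of consent are kept and used. Bring 3.2.4 into line, so that use of these data no longer depends on case-by-case judgement.

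State how an incomplete final window and a missing responder status are handled. One suitable choice is a repeated-measures model over the three 28-day treatment periods with baseline MMD, treatment, period and their interaction. The final-period contrast would be primary, which leaves the endpoint unchanged. Patients without a final value would count as non-responders. Other methods would serve if fixed before unblinding.

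Cost: wording and slightly more analysis, with no new data, because the diary already runs daily for 12 weeks. The model relies on data being missing at random. When placebo dropout was instead driven by the final-period outcome itself, an analysis using the earlier months also missed the assumed −2.0, averaging −1.56 to −1.62. One sensitivity analysis with a pessimistic assumption for the missing values should therefore accompany it.
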